# A randomized controlled trial of a skills training for oncologists and a communication aid for patients to stimulate shared decision making about palliative systemic treatment (CHOICE): study protocol

**DOI:** 10.1186/s12885-017-3838-8

**Published:** 2018-01-08

**Keywords:** Shared decision making, Advanced cancer, Palliative medicine, Systemic treatment, Doctor-patient communication, Patient participation, Patient education, Skills training

## Abstract

**Background:**

Systemic treatment for advanced cancer offers uncertain and sometimes little benefit while the burden can be high. Hence, treatment decisions require Shared Decision Making (SDM). The CHOICE trial examines the separate and combined effect of oncologist training and a patient communication aid on SDM in consultations about palliative systemic treatment.

**Methods:**

A RCT design with four parallel arms will be adopted. Patients with metastatic or irresectable cancer with a median life expectancy <12 months who meet with a medical oncologist to discuss the start or continuation of palliative systemic treatment are eligible. A total of 24 oncologists (in training) and 192 patients will be recruited. The oncologist training consists of a reader, two group sessions (3.5 h; including modelling videos and role play), a booster feedback session (1 h) and a consultation room tool. The patient communication aid consists of a home-sent question prompt list and a value clarification exercise to prepare patients for SDM in the consultation. The control condition consists of care as usual. The primary outcome is observed SDM in audio-recorded consultations. Secondary outcomes include patient and oncologist evaluation of communication and decision-making, the decision made, quality of life, potential adverse outcomes such as anxiety and hopelessness, and consultation duration. Patients fill out questionnaires at baseline (T0), before (T1) and after the consultation (T2) and at 3 and 6 months (T3 and T4). All oncologists participate in two standardized patient assessments (before-after training) prior to the start of patient inclusion. They will fill out a questionnaire before and after these assessments, as well as after each of the recorded consultations in clinical practice.

**Discussion:**

The CHOICE trial will enable evidence-based choices regarding the investment in SDM interventions targeting either oncologists, patients or both in the advanced cancer setting. The trial takes into account the immediate effect of the interventions on observed communication, but also on more distal and potential adverse patient outcomes. Also, the trial provides evidence regarding the assumption that SDM about palliative cancer treatment results in less aggressive treatment and more quality of life in the final period of life.

**Trial registration:**

Netherlands Trial Registry number NTR5489 (prospective; 15 Sep 2015).

**Electronic supplementary material:**

The online version of this article (10.1186/s12885-017-3838-8) contains supplementary material, which is available to authorized users.

## Background

World-wide, 8.2 million people die of cancer each year [1]. In the final period of life, disease-targeted treatment offers uncertain and sometimes little benefit while the burden of treatment can be high. Hence, treatment decisions are highly preference-sensitive [2]. Decision making cannot be based solely on evidence and patients’ clinical status, but should incorporate patients’ values and preferences [3]. This requires shared decision making (SDM), an approach whereby clinician and patient exchange information and jointly deliberate to come to an agreed-upon decision [4–6]. SDM is increasingly advocated because of the ethical imperative to involve patients [7] as well as the increasing evidence for beneficial patient outcomes, such as satisfaction with communication and well-being [8, 9]. Moreover, yet tentatively, SDM in the final period of life might result in more attention to symptom control and less (aggressive) medical interventions [10–12]. For example, in the curative setting, the use of patient decision aids resulted in reduced choice of invasive surgery and screening [13].

### Decision making in advanced cancer

SDM implies that clinicians provide accurate and balanced information about the available treatment options and invite patients to express their values and preferences [14]. In consultations with advanced cancer patients, such a two-way flow of information is not always achieved. Oncologists’ information provision is often incomplete, e.g., oncologists infrequently discuss the expected survival benefits of palliative systemic treatment or the option to refrain from systemic treatment [15–17] and communication about prognosis and death is often implicit [18, 19]. Moreover, a recent study demonstrated that joint elaboration and preference construction is not standard practice [20], particularly once systemic treatment has started.^.^ In sum, systemic treatment for advanced cancer may be prescribed and continued without conscious and joint deliberation.

Several factors make SDM particularly challenging in consultations with advanced cancer patients. SDM requires high-level communication skills known to be demanding for clinicians, such as tailoring information provision to the individual patients’ information needs [21, 22], dealing with patients’ emotions in response to bad news [23] and coaching patients in constructing a treatment preference. Furthermore, SDM puts patients in an active and participatory role. Given the complexity and significance of the topics discussed in consultations about treatment for advanced cancer, as well as the highly vulnerable and dependent position of patients, this may be challenging [24]. Lastly, SDM can be particularly sensitive in this context as it deals with the imminent end of life. Both oncologists and patients have been shown to prefer to keep a focus on the short term and on ‘beating’ the cancer, instead of anticipating what is to come [25–27]. Such focus may enable the patient to retain a sense of hope, even if misguided, and an often desired ‘fighting spirit’. At the same time, it may prevent decisions in keeping with the patient’s preferences.

### Training oncologists

Commonly, the performance of providers is addressed to enhance communication in medical encounters [28–30]. It has been shown that training significantly improves the observed communication skills in simulated settings as well as in clinical practice on the short term [31–34]. However, there is much less evidence for the consolidation of this effect on the long-term and for an effect on more distal patient outcomes. Reviews demonstrated that training programs specifically focused on SDM vary widely in format and components with little robust evidence for efficacy [35–37]. Common components are role play, discussion, education in small groups, printed materials, and audit/feedback [35]. Effective means are small trainee groups; an experienced trainer and booster sessions to refresh training content [33, 38]. The evidence for a dose-response relationship is not conclusive [32, 38], although it has been suggested that training for minimally 3 days is more likely to result in behavior change [33]. To our knowledge, no training program has explicitly focused on teaching SDM about palliative cancer treatment. The current trial examines the effect of a training that aims to increase SDM regarding palliative systemic treatment through addressing medical oncologists’ knowledge, beliefs and skills. It combines printed material, video modelling, education, small groups discussion, role play, and a booster session.

### Supporting patients

Besides training providers, there is growing evidence for patient-targeted communication support to improve communication. Interventions targeting patients were shown to enhance patient participation in oncology consultations in general [39], as well as in the palliative setting [30, 40]. Moreover, there is evidence suggesting that preparing patients can improve SDM in consultations [41], although the effect may be smaller than the effect of provider-targeted interventions [37]. A well-known and widely implemented tool to support patients in decision making is a decision aid (DA). A DA usually presents treatment options as well as the pros and cons of the options in paper or digital format, and offers value clarification exercises that help patients formulating a treatment preference [42, 43]. A DA can be used independently by patients, but use of the aid in or next to a conversation with a care provider is recommended [44, 45]. DA’s have been developed for the advanced cancer setting [46–48]. These studies report on a positive effect on patients’ understanding, but not on the decision made, patients’ decisional role and post-decision confidence. Another well-known patient-targeted communication tool is a Question Prompt List (QPL), a structured booklet with example questions patients can ask their doctor. A QPL is shown to facilitate cancer patients’ participation in consultations [49]. It stimulates agenda setting, assists patients in formulating and remembering important questions, and helps to put difficult issues on the agenda. Moreover, a QPL gives patients control over the oncologist’s information provision and enhances information giving about topics oncologists regularly fail to address, such as prognosis [50]. A QPL focused on end-of-life issues for patients with incurable cancer proved to be an acceptable tool in consultations with a medical oncologist [51–53].

The current study examines the effect of a communication aid focused on SDM about palliative systemic treatment that combines elements from both DA’s (value clarification exercises) and QPL’s (question prompts). It can be used flexibly regardless of the type and number of available treatment options, and explicitly targets the two-way flow of information within a conversation between patient and oncologist.

### Targeting both parties

Leaving out one party in a communication intervention might be similar to ‘anticipating an elegant waltz to emerge on the ballroom when only one partner has taken dance lessons’ [54]. Indeed, interventions to improve communication may be most effective if they target both doctors and patients [30, 37]. Focusing only on patients and not on doctors might even have unintended negative effects [55–57]. For instance, Australian breast cancer patients who received a preparation package (including a QPL) participated more actively in the consultation than women who did not receive such a package. However, they were less likely to reach their preferred level of involvement in the consultation [56]. Similarly, another Australian study showed that providing cancer patients with a QPL which was not actively endorsed by the oncologist, did result in more observed patient participation, but also in longer consultations and more patient anxiety post-consultation [58]. Recently, it was shown that the combination of a skills training for oncologists and a coaching session including a QPL for advanced cancer patients improves patient-centered communication, yet not secondary outcomes such as quality of life and care received at the end of life [59, 60]. To the best of our knowledge, no studies have examined the independent and combined effect of a patient- and an oncologist-targeted intervention on SDM in consultations with advanced cancer patients.

### Aims

The aim of the CHOICE trial (CHOosing treatment together In Cancer at the End of life) is to evaluate the effectiveness of a patient communication aid and an oncologist training on shared decision making regarding palliative systemic treatment for cancer patients with an estimated life expectancy of <1 year. The *primary outcome* is observed SDM in decision-making consultations. We hypothesize that each of the interventions will separately improve observed SDM and that the combination of both will be more effective in improving observed SDM than targeting only one party.

For secondary outcomes, we hypothesize a positive effect of the interventions on immediate outcomes related to communication and decision making. We expect the oncologist training to improve observed SDM in standardized patient assessments as well as observed general communication skills in standardized and in actual encounters. Furthermore, we hypothesize a positive effect of the interventions on patients’ perceived efficacy, satisfaction, perceived empathy, achievement of the preferred role in decision making, perceived shared decision making, evaluation of the decision made and patients’ trust in the oncologist and oncologists’ post-consultation satisfaction. Moreover, we hypothesize an effect of the interventions on *distal outcomes*, i.e., the decision made, patients’ attitude towards length or quality of life, and patients’ quality of life. We will also explore the effect of the interventions on *potentially adverse outcomes*, i.e., patients’ anxiety, loss of fighting spirit and hope. Lastly, we will explore the effect of the interventions on consultation duration and examine patients’ use and evaluation of the communication aid.

## Methods/design

This protocol is written in accordance with the CONSORT statement for reporting parallel group randomized trials [61].

### Design

The study adopts a randomized controlled trial design with four parallel arms. Medical oncologists (in training) will be randomized to receive the training or to continue their standard practice. Patients (within oncologists) will be randomized to either receive the communication aid or care as usual.

### Study setting

The study will be conducted on medical oncology departments of both academic and non-academic hospitals in the Netherlands.

### Participants

The source population consists of (1) all patients with metastatic or inoperable tumors for whom survival curves indicate a median life expectancy of <12 months without disease targeted treatment, for whom systemic palliative treatment does not offer median survival benefit of >6 months (at group-level), who meet with the oncologist to discuss either the start of (a new line) of treatment or the (dis)continuation or adjustment of current treatment, and (2) medical oncologists as well as medical oncologists in training who communicate with these patients in decision-making consultations. Eligible are all oncologists (in-training) who are qualified to communicate with patients independently. Oncologists involved in the design of the interventions will be excluded. Eligibility criteria for patients are presented in Table 1. For some patients, eligibility for systemic treatment (yes, no or unsure) could only be assessed during the consultation (exclusion criterion 5 and 6). As a result, some patients will be judged non-eligible and will be excluded post-hoc (i.e., after randomization and first data collection).

**Table 1 Tab1:** Patient eligibility criteria

*Patient inclusion criteria*	
1. patients diagnosed with metastatic or locally irresectable cancer 2. not eligible for treatment with curative intent 3. a median life expectancy of < 1 year without systemic treatment, and a median survival benefit of systemic treatment of < 6 months, which includes, but is not limited to: a. patients with metastases or locally irresectable tumors of the pancreas, esophagus, stomach, liver, (gall) bladder, and patients with metastatic sarcoma or melanoma b. patients with advanced cancer, irrespective of tumor type, who have experienced progression under first line palliative systemic treatment. 4. scheduled for a consultation with a participating medical oncologist (in training) in which decisions about the start, (dis)continuation or adjustment of palliative systemic treatment will be made. This includes: *a. initial consultations* in which a decision to start, forego or postpone a (new line of) systemic treatment will be made *b. evaluative consultations* in which current treatment is evaluated, usually after a fixed number of cycles (with a CT/PET-CT) and a decision to (dis)continue and/or adjust systemic treatment will be made	
*Patient exclusion criteria*	
1. patients who have insufficient mastery of Dutch to understand the communication aid and questionnaires as judged by either the physician or the researcher 2. cognitive disabilities or a psychiatric disorder that hinder understanding of the communication aid and questionnaires as judged by either the physician or the researcher 3. insufficient time between identification and consultation (< 2 working days) 4. a primary brain tumor or brain metastasizes which significantly hinder cognitive functioning 5. not/no longer/not yet eligible for (an additional line of) palliative systemic treatment (standard or experimental), which prevented discussion of systemic treatment as judged by the physician 6. insufficient diagnostic information available, which prevented discussion of systemic treatment as judged by the physician	

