#### Patients

Patients are randomized to receive the communication aid or ‘usual care’. Randomization is performed in ALEA software for randomization in clinical trials. Randomization stratifies for three factors: (1) the condition of the treating oncologist (trained/untrained) and (2) working experience of the treating oncologist (staff/in training) and (3) the type of consultation (initial treatment planning consultation/evaluative consultation), to ensure an equal ratio in all study arms. Stratification occurs through minimization. Stratification factor 1 (trained or untrained oncologist) receives a weight of 3; factors 2 and 3 a weight of 1. A biased coin of 5 starts to work in case of a contrast of >3 between the two conditions. Randomization data in ALEA are adjusted in three specific scenarios: (1) to change the status and experience of the treating oncologist in case patients switch oncologists after randomization, (2) exclusion of a randomized patient in case the patient does not provide final written informed consent (see Procedure) and (3) exclusion of a randomized patient if only during the consultation it turns out the patient does not meet the eligibility criteria (see Participants). These adjustments will be performed and documented by an independent methodologist.

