### Blinding

*Oncologists* are not blinded for their own condition. Although they are blinded for their patients’ condition, the communication aid may come up in the consultation. They will be asked whether they know or suspect the patient to have received the aid in the questionnaire (T2) right after the consultation. *Patients* are obviously not blinded for whether they received the aid or not. They are blinded for their oncologist’s condition though. *Outcomes assessors* are blinded for the condition of the oncologist. The assessors will not be informed about the patients’ condition either, yet the aid may come up in the consultation.

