### Statistical methods

#### Primary outcome

To account for the hierarchical nature of the data, i.e. patients nested within oncologists, multilevel regression analysis will be used to test the effect of the single interventions on the observed level of SDM in the audio-recorded consultation. Analysis will be conducted separately for the OPTION12 and the 4SDM. Random intercept and slope models will be examined. The effect of the oncologist training (level of oncologists) will be established among patients who did not receive a communication aid. The effect of the communication aid (level of patients) will be established among patients of untrained oncologists. Effects with two-sided *p*-values < .05 will be considered significant; 95CI’s as well as effect sizes will be provided. As the OPTION12 is currently the most widely used instrument to assess SDM, an intervention will be considered effective if it had a significant effect on OPTION12 scores. Baseline differences across arms on background characteristics (patient age, gender, educational level) as well as patients’ baseline measures will be examined with the appropriate statistical tests (ANOVA, Chi-squared tests). All analyses of effectiveness will be controlled for differences between arms at baseline as well as the two stratification variables (working status oncologist, type of consultation). All analyses will be intention-to-treat, i.e., all eligible consultations will be included in the analysis (irrespective of whether the communication aid was actually received or read; or whether the oncologist received the full training package).

The hypothesized additional effect of the combined intervention will most likely be smaller than the effects of the single interventions (RQ1). That is, combining the two is hypothesized to increase but not to double the effect of the single interventions. The combination of the training and the aid will be considered more effective than either or both single interventions if (1) the effect size of the combination compared to care as usual is statistically significant and (2) is at least 150% of the effect size of either or both single interventions. The study is not powered to statistically test the difference between the combination and the single interventions.

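### Patients are removed after the outcome consultation, partly on the treating oncologist's view of whether discussion was prevented, and the remaining set is not intention-to-treat

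*Protocol article*

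**What the plan says.** Participants states that for some patients "eligibility for systemic treatment (yes, no or unsure) could only be assessed during the consultation", and refers to exclusion criteria 5 and 6. It continues: "As a result, some patients will be judged non-eligible and will be excluded post-hoc (i.e., after randomization and first data collection".

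In Table 1 both criteria have two limbs. The first is factual: the patient is not eligible for a (further) line of palliative systemic treatment (criterion 5), or diagnostic information is insufficient (criterion 6). The second is shared: "which prevented discussion of systemic treatment as judged by the physician".

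Randomization, Patients lists when the randomisation data are adjusted. One case is "exclusion of a randomized patient if only during the consultation it turns out the patient does not meet the eligibility criteria". An independent methodologist carries out and records these adjustments. Another case is "exclusion of a randomized patient in case the patient does not provide final written informed consent".

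Under Blinding, oncologists "are not blinded for their own condition". On the patient's arm it says: "Although they are blinded for their patients’ condition, the communication aid may come up in the consultation".

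Statistical methods, Primary outcome, defines the analysis set: "All analyses will be intention-to-treat, i.e., all eligible consultations will be included in the analysis".

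**The concern.** The exclusion is decided after both interventions have been delivered and at the same consultation that yields the primary outcome. One of its two limbs concerns what could be discussed there. The training teaches oncologists to set the agenda for shared decision making, to present options and to make or defer a decision in agreement. The aid gives patients questions about foregoing or postponing treatment and about experimental treatment. With the same medical file, a trained oncologist or a prompted patient may discuss options where another pair would not. Whether the consultation is kept can then depend on arm, and the person who decides is not blind to the training.

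At stake are the comparability of the arms in the primary analysis and the claim that this analysis is by intention to treat. A set formed after randomisation by a judgement related to the outcome does not have the protection that this label implies.

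**Working it through.** **Order of events.** Training precedes the recorded consultations (Procedure and time line). The aid is sent after oral consent and randomisation (Recruitment, Patients). Eligibility under criteria 5 and 6 is then judged during the consultation (Participants), and the same consultation is scored (Outcomes, Primary outcome). The judgement therefore follows both interventions. The methodologist's stated task is to adjust the randomisation data and document this; judging eligibility is not part of it.

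**Reproducing the planned power.** Inputs from Sample size: d = 0.8, ICC = 0.20, two-sided alpha 0.05, 12 oncologists per arm, 8 patients each, power 0.84. The training effect is tested only in patients without the aid, so m = 4 per oncologist if the split is even.
- Design effect = 1 + (m − 1) × ICC = 1 + 3 × 0.20 = 1.6.
- Effective n per arm = 12 × 4 / 1.6 = 30.
- SE in SD units = √(2/30) = 0.258.
- Noncentrality = 0.8 / 0.258 = 3.10. With 24 − 2 = 22 df, power = 0.842, which matches 0.84.

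**Illustration of bias.** The documents give no exclusion rate, so all rates here are assumptions. If a share p of an arm is removed and those consultations lie 1 SD below the arm's average, the retained mean rises by p/(1 − p) SD.
- 5% removed: 0.05/0.95 = 0.053.
- 15% removed: 0.15/0.85 = 0.176. Shift of the contrast = 0.176 − 0.053 = 0.124 SD, or 15% of 0.8.
- 20% removed: 0.20/0.80 = 0.250. Shift against 5% = 0.197 SD.
- Equal removal and equal selection: shift 0.

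**Direction.** If training or the aid makes retention more likely, the comparator arm loses more low-scoring consultations. Its mean rises and the estimated effect shrinks.
- True effect 0.8, shift 0.124: noncentrality = (0.8 − 0.124)/0.258 = 2.62, power about 0.71.
- True effect zero, same shift: noncentrality 0.48 in size. Total two-sided error is about 7.4%, of which 6.7% favours the comparator. False claims of benefit fall from 2.5% to about 0.8%.

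These figures keep the effective n at 30, as if removed patients were replaced. Without replacement, the loss of numbers alone gives power 0.832 at 5%, 0.810 at 15% and 0.797 at 20% removed in both arms.

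**Weaker selection.** Suppose instead that the judgement correlates with the score at r = 0.3 to 0.7. The retained mean then rises by r × φ(z)/(1 − q), with q the share removed, z the matching normal quantile and φ the normal density. At 15% this is 0.274r and at 5% 0.109r. The difference, 0.166r, is 0.05 to 0.12 SD. For 20% against 5% it is 0.07 to 0.17 SD. The 1 SD illustration therefore sits at or slightly above the top of these ranges.

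**The case against.** The strongest reply starts from Table 1. An oncologist who merely fails to raise the options does not meet criterion 5 or 6, because the factual limb must also hold. The second limb narrows exclusion: a patient who is ineligible, but with whom treatment was discussed, stays in. This stands, and it limits the room for arm-dependent judgement. It does not remove it, because among patients who meet the factual limb the second limb still decides who is kept.

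Second, the aid is tested only among untrained oncologists, so training status is constant in that comparison and the oncologist is nominally blind to the patient's arm. This also stands. A reader might infer that both primary comparisons are certainly biased; the text supports only that they could be, the aid comparison less directly. The Discussion does concede that oncologists are probably not blind to the patient's arm.

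Third, a reader might infer an inflated risk of falsely claiming benefit. The documents do not support that. Under the mechanism that the interventions themselves suggest, most of the extra error lies in the tail against the intervention. The opposite direction would need a mechanism that the text does not supply.

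Fourth, the exclusions are disclosed, the intention-to-treat set is spelled out, and a flow diagram or analysis plan may show exclusions by arm. Their absence from the article is no fault. The rule and the label, however, are stated in the article, and the limitations in the Discussion do not name this exclusion.

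**Conclusion.** The point holds in limited form. Randomised patients leave the analysis after the outcome consultation, partly on a judgement about discussion by an oncologist who knows the training allocation. The set described under Statistical methods is therefore modified intention-to-treat at best. Bias is possible in the training comparison and, less directly, in the aid comparison. Its direction and size cannot be derived from the documents. It is nil with equal removal and equal selection; at the assumed 5% against 15% it is about 0.05 to 0.12 SD, depending on how strongly the judgement follows the score. At the upper figure, power falls to about 0.71 if the shift runs against the intervention. The case for change rests on the rule and the label, not on these assumed rates.

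A reader might also infer that the file as it stood before the consultation could settle eligibility. Participants says that for these patients it could only be assessed during the consultation, so that route is not open.

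**What to change.** - In Table 1, let exclusion after randomisation rest only on the factual limb of criteria 5 and 6: eligibility for a further line, and availability of the required diagnostic results. Use clinical facts documented in the medical file up to and including the consultation date. Drop prevented discussion as the test.
- Have each such exclusion confirmed before outcome coding by an existing team member who is blind to both allocations and had no contact with the patient. The second condition matters because a research associate may sign the consent form with a patient who has been told the allocation.
- Under Statistical methods, call the main set modified intention-to-treat. Add a sensitivity analysis of the primary outcome in all randomised, consented patients with a recording, and show exclusions by arm.

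The cost is a reworded table and analysis set, a little extra file checking, and coding of some recordings already made. A few consultations without a real decision may stay in and dilute the effect slightly.
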